# Monetary costs of Alzheimer’s disease in China: protocol for a cluster-randomised observational study

**DOI:** 10.1186/s12883-017-0802-9

**Published:** 2017-01-25

**Keywords:** Alzheimer’s, Dementia, Cost of illness, Healthcare cost, Observational study

## Abstract

**Background:**

Alzheimer’s disease (AD) is the most common type of dementia. International multilateral cost-of-illness (COI) studies have revealed that the cost of treating this disease is huge, which places a significant burden on patients’ families and their healthcare systems. However, no such studies have been conducted in China. This study estimates the monetary costs of patients with AD in mainland China.

**Methods:**

This study planned to start in October 2015 and to finish in March 2016. It covered 30 provincial, municipal, and autonomous regions in mainland China. The sites and research centres in each region were selected randomly. The participating sites include Tier 3 hospitals, psychiatric hospitals, geriatric hospitals, nursing homes, and residences. More than 2500 patients with AD and their caregivers from all of the 81 research centres will be enrolled to fulfil the calculated sample size. The monetary costs of AD, which include direct medical costs, direct non-medical costs, and indirect costs, are being collected using the electronic medical record system and residence health system at each site; face-to-face interviews are being performed when necessary. Descriptive statistics will be used to summarise the patient characteristics and generalised linear models will be developed to calculate the costs.

**Results:**

The main findings will include national and per patient annual monetary costs of AD in China.

**Conclusions:**

To the best of our knowledge, this is the first large-scale cluster-randomized observational study to estimate the economic burden of AD in Chinese patients. The methodology used was based on China’s current healthcare system and is suitable for the purpose of the study. Because the burden of AD on patients, families, healthcare providers, and society is substantial and increasing, it is important and necessary to understand the economic burden caused by this disease.

**Trial registration:**

Our trial was retrospectively registered on ClinicalTrials.gov, NCT02694445, registered on 02/26/2016

## Background

The Chinese population is rapidly aging. The sixth national population census showed that there were 178 million people aged ≥ 60 years in China, accounting for 13.26% of the total population [1]. The incidence of senile dementia (age of onset ≥65 years) is ~6%, with Alzheimer’s disease (AD) being the most common form, accounting for ~65% of cases [2–5]. In 2014, an epidemiological study that encompassed 30 cities/towns and 45 rural areas from 5 representative Chinese provinces demonstrated that the incidence of dementia and AD in people aged ≥65 was 5.14 and 3.21%, respectively. Furthermore, the prevalence was significantly higher in rural areas compared to urban populations [6].

The monetary costs of AD have been studied worldwide. International multilateral cost-of-illness (COI) studies can identify and measure all of the costs associated with any specific disease including the direct, indirect, and intangible costs; [7] such studies were designed to provide an estimate of the economic burden of disease [7]. A recent study indicated that the cost of AD is substantial and increases with disease severity [8]. Between 2009 and 2010, a cross-sectional survey conducted in the United Kingdom, which included 249 AD patients from 18 cities, revealed that the total monetary costs of AD were ~ £4000 per citizen every 3 months [9]. Moreover, the annual costs associated with AD were $100 billion in the United States, of which $24.6 billion was for healthcare (including caregiver burden and the cost of medical care) [10]. In 2014, a French study showed that the average total monthly costs of AD were €2450 using the proxy good method, and €3102 using the opportunity cost method [11]. In the same year, a study in Finland indicated that the medical costs of an AD patient were €23,059 per person per year [12]. Thus, AD creates a heavy burden to both patients’ families and society and is also a huge challenge to economic development and elderly healthcare. However, to date, studies on the monetary costs of AD have mostly been performed in developed countries such as the United States and United Kingdom, and there have been no large-scale national surveys on the economic burden caused by this disease in developing countries such as China. Because the burden of AD on patients, families, healthcare providers, and society is substantial and increasing [13, 14], our large-scale national study in China is important and necessary.

## Methods

### Study design

This study is a multicentre study with a large sample size that began in October 2015. Before beginning the study, the protocol and case report form (CRF) were designed using an operator manual, and advice was sought from international scholars. The study design and procedures are illustrated in Fig. 1.

**Fig. 1 Fig1:**
[figure not shown]
Flow chart of the monetary costs of Alzheimer’s disease in China. *Note:* n_1_, the number of research centres; n_2_, the number of patients with AD

### Distribution of investigation sites and inclusion criteria

This study covered 30 provincial, municipal, and autonomous regions in mainland China, with the exception of Tibet, Hong Kong, and Macao. The target sites included Tier 3 hospitals, mental health centres/psychiatric hospitals, gerontology hospitals, nursing homes/gerocomiums/care facilities, and both urban and rural residences. The study sites in each region were selected randomly. However, each site must meet the following pre-specified criteria: (1) Tier 3 general hospitals, mental health centres, psychiatric hospitals or gerontology hospitals with memory clinics, dementia specialists, psychological evaluation divisions, AD-relevant diagnostic equipment (e.g., computed tomography [CT], 1.5 T or above magnetic resonance imaging [MRI]), and laboratories with the ability to examine samples that may aid in the diagnosis of AD. (2) Nursing homes/gerocomium/care facilities with dementia specialists, >100 beds, and the ability to admit patients with AD. (3) Residences with >500 residents, a residence health system (e.g., electronic health records), active resident or village committees, and staff who can assist with the study. (4) Patients who fully understand the protocol and agree to participate in the study.

The study included 81 research centres that meet the inclusion criteria (Fig. 2).

**Fig. 2 Fig2:**
[figure not shown]
The distribution of investigational centres in China. *Notes:* 01, Anhui Province; 02, Beijing City; 03, Fujian Province; 04, Gansu Province; 05, Guangdong Province; 06, Guangxi Autonomous; 07, Guizhou Province; 08, Hainan Province; 09, Hebei Province; 10, Henan Province; 11, Heilongjiang Province; 12, Hubei Province; 13, Hunan Province; 14, Jilin Province; 15, Jiangsu Province; 16, Jiangxi Province; 17, Liaoning Province; 18, Inner Mongolia Autonomous; 19, Qinghai Province; 20 Shandong Province; 21, Shanxi Province; 22, Shaanxi Province; 23, Shanghai City; 24, Sichuan Province; 25, Tianjin City; 26, Xinjiang Autonomous; 27, Yunnan Province; 28, Zhejiang Province; 29, Chongqing City; 30, Ningxia Autonomous

### Criteria for AD patients

Because we investigate the direct and indirect monetary costs of AD, strict inclusion and exclusion criteria for AD are essential. The following patients are being included: those who are newly diagnosed with AD in this study or who have been previously diagnosed, patients aged ≥ 60 years with normal or corrected vision and hearing, and those who are able to provide an informed consent form signed by himself/herself or a legal guardian. Dementia is diagnosed according to the criteria described by the Diagnostic and Statistical Manual of Mental Disorders, Fourth Edition, Text Revision (DSM-IV-TR) [15]. The diagnosis of AD is made using the National Institute of Neurologic and Communicative Disorders and Stroke and the Alzheimer’s Disease and Related Disorders Association (NINCDS-ADRDA) [16]. The diagnosis also required to meet the following: a Modified Hachinski Ischemic Scale (MHIS) score ≤ 4 [17], an Activity of Daily Living Scale (ADL) score ≥ 23 [18], and a Geriatric Depression Scale (GDS) score < 11 [19]. Neuroimaging MRI is used to support the AD diagnosis (atrophy in the medial temporal lobe and a white matter lesion score ≤ 2 according to the Fazekas criteria) [20, 21]. The severity of AD is estimated according to the mini-mental state examination (MMSE) scale [22] (for illiterate dementia mild, 21–24 points; moderate, 11–20; severe, ≤10. For literate dementia: mild, 16–19 points; moderate, 8–15; severe, ≤7). The diagnosis of AD is confirmed by brain CT or MRI scans and laboratory tests to rule out any significant comorbidities. Patients will be excluded if they meet any of the following criteria: presence of vascular dementia or dementia caused by other factors such as major depression or other major psychiatric illnesses, thyroid dysfunction, encephalitis, multiple sclerosis and other dementias such as frontotemporal dementia (FTD) [23], dementia with Lewy bodies (DLB) [24], and Parkinson’s dementia (PD); [25] when MRI and laboratory tests (e.g., blood cell counts, liver and renal function tests) did not support or rule out a diagnosis of AD; and a history of alcoholism or drug abuse.

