### Sample size

The sample size was calculated using the equation, $$ n=\frac{U_{1-\alpha /2}^2{S}^2}{\delta^2} $$ where *S* was the stand division and *δ* was the allowable error. The planned sample size was generated based on previous data obtained from an economic evaluation of an AD-type dementia study [26]. Based on the standard deviation (SD) of AD-related costs per patient per year (11,037) and an allowable error of 500, the total sample size required was 1,872. Therefore, the planned total sample size in this study was ~2,500 to allow for a defective rate of 25%. Before starting the study, information was surveyed from all randomly selected participating sites, including the number of dementia physicians at each site, the number of AD patients, and the proportion of outpatients and inpatients in the last year. Based on these data 20–40 patients with AD will be assigned for each site. The sites include hospitals (Tier 3 hospitals, gerontology hospitals, mental health centres and psychiatric hospitals), nursing homes, gerocomiums, care facilities, and residences.

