#### Calculation of costs due to AD

Different distributions will be considered for the monetary costs associated with AD, including normal, lognormal, exponential, and gamma. To compare the costs of different subgroups, *t*-tests or Kruskal-Wallis analysis of variance will be used. For base case analyses, GLMs will be developed using the gamma distribution with a log-link function [35]. Models will be developed with the total cost per person per year as the dependent variable, and independent variables will be selected using a backward selection method (*P* > 0.05 for removal), with patient age, patient sex, and MMSE severity all forced to remain in the model. Considering the diverse of research centres sites, we also added the sites as a covariant in the analysis. The variables used for backward selection will be years of formal education, time since AD diagnosis, marital status, location of residence (urban or rural), number of children, baseline MMSE score, baseline ADL score, the number of caregivers, the number of comorbidities, and caregiver demographics.

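### The printed MMSE severity bands look exchanged between illiterate and literate patients and leave eligible scores without a class, although severity is a forced covariate in the base-case cost model

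*Protocol article*

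**What the plan says.** Criteria for AD patients names the instrument: "The severity of AD is estimated according to the mini-mental state examination (MMSE) scale". It then gives two sets of bands: "for illiterate dementia mild, 21–24 points; moderate, 11–20; severe, ≤10. For literate dementia: mild, 16–19 points; moderate, 8–15; severe, ≤7". The article does not restate or correct them anywhere else.

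The same section sets scale limits for the diagnosis: "a Modified Hachinski Ischemic Scale (MHIS) score ≤ 4 [17], an Activity of Daily Living Scale (ADL) score ≥ 23", together with a GDS limit of below 11, DSM-IV-TR and NINCDS-ADRDA criteria, and imaging. None of these is an MMSE limit.

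Calculation of costs due to AD describes the base-case model, a gamma GLM with log link for total cost per person per year, "with patient age, patient sex, and MMSE severity all forced to remain in the model". Education and the raw MMSE score enter only as candidates that may be removed: "The variables used for backward selection will be years of formal education, time since AD diagnosis, marital status", with baseline MMSE score later in the same list.

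**The concern.** The evident reason for splitting MMSE bands by literacy is that people without schooling lose points on reading, writing and calculation at the same degree of impairment. Their cut-offs should then be lower. The printed bands put them higher, so an illiterate patient is called more severe than a literate patient with the same score.

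The bands also do not cover the patients who can enter. The literate set ends at 19 and the illiterate set at 24, while eligibility does not depend on the MMSE.

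At stake is the meaning of the severity term in the base-case model. The Background cites evidence that cost rises with severity, and recruitment from urban and rural residences makes it likely that literacy varies in the sample. A severity class whose meaning depends on literacy mixes the severity coefficient with education, and backward selection cannot remove the term.

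**Working it through.** **Inputs.** The two printed sets of bands; the absence of an MMSE entry limit (both in Criteria for AD patients); the forced severity term (Calculation of costs due to AD). The MMSE is taken to run from 0 to 30 in whole points.

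**The plan's own figure.** No calculated figure in the article depends on the bands. The one it does state, the sample size, reproduces: with "standard deviation (SD) of AD-related costs per patient per year (11,037) and an allowable error of 500" and a two-sided alpha of 0.05 (assumed, as no value is given), n = 1.96² × 11,037² / 500² = 1,871.8 with unrounded z, rounded up to 1,872; 1,872 / 0.75 = 2,496, about 2,500. Nothing below changes it.

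**Step 1. Assign every score under the printed bands.**

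| MMSE score | Number of scores | Illiterate | Literate |
|---|---|---|---|
| 0–7 | 8 | severe | severe |
| 8–10 | 3 | severe | moderate |
| 11–15 | 5 | moderate | moderate |
| 16–19 | 4 | moderate | mild |
| 20 | 1 | moderate | no class |
| 21–24 | 4 | mild | no class |
| 25–30 | 6 | no class | no class |

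The groups agree at 0–7 and 11–15. At 3 + 4 = 7 scores (8–10 and 16–19) the illiterate patient is graded one class more severe. Scores without a class: 1 + 4 + 6 = 11 for literate patients (20–30) and 6 for illiterate patients (25–30).

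**Step 2. Exchange the labels.** The two right-hand columns swap. The class then changes wherever the columns differ: 3 + 4 + 1 + 4 = 12 of the 25 scores from 0 to 24, in each group. Seven of the 12 are one-class shifts, in opposite directions for the two groups. The other five (20–24) are moves between a class and no class: literate patients gain one (20 moderate, 21–24 mild) and illiterate patients lose one. Scores 25–30 stay unclassed for both groups.

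**Step 3. Trace where severity is used.**
- Base-case GLM of total cost per person per year: severity is forced in.
- GLMs for costs attributable to AD (Nationwide cost due to AD): the listed covariates are coexisting conditions and demographics, including education; severity is not listed.
- Total cost per patient per year: a sum of cost components; severity is not used.
- National cost: patient numbers times mean costs by treated or untreated and inpatient or outpatient status; severity is not used.

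So the bands act on one model. The article gives no distribution of MMSE scores or of literacy, so neither the number of patients affected nor the change in any coefficient can be derived.

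**The case against.** The strongest reply is that this may be a slip in a journal article. The CRF, training material and analysis code are not shown and may carry the right labels. That stands: a reader might infer that severity in the study data is already wrong, but the article shows only that following its stated rule would make it wrong.

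The direction of the error also rests on general reasoning about schooling and MMSE scores; the article does not give its reason for the split, and the cited scale source is not at hand. That is why the exchange is called probable. The coverage gap does not need this argument: eligible scores have no class under either labelling.

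Four stronger readings are tempting and not supported:
- That severity enters all the cost models, or that the main results are biased. Step 3 shows one model affected and the per-patient and national totals untouched.
- That unclassed patients would be dropped as missing. The article gives no rule; they might equally be classed ad hoc.
- That 12 of 25 scores measures the bias. It counts scores, not patients or cost.
- That exchanging the labels settles the matter. It moves the 20–24 gap to illiterate patients and leaves 25–30 open for everyone.

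Finally, years of education and raw MMSE may stay in the model and absorb part of the distortion. They are removable candidates, so this cannot be relied on.

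**Conclusion.** The point holds as a defect in a stated classification rule. The literacy labels run against the purpose of having them, and the classes do not cover all scores that eligible patients may have. If the bands are applied as printed, the forced severity covariate in the base-case model is graded one class apart between literacy groups at seven scores, and has no value for literate patients at 20–30 and illiterate patients at 25–30.

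This rests on two assumptions: that literacy-specific bands are meant to allow for lower scores without schooling, and that the printed rule is the one used. It does not call the headline cost totals or the sample size into question, and the direction and size of any change in the model coefficients are unknown. It should be settled before that model is fitted.

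**What to change.** 1. Check both sets of bands against the CRF and the cited MMSE source, and correct the labels if they were exchanged.
2. Define illiterate from the recorded education data. The article lists education level and years of formal education but not literacy status, so the recode needs this rule first.
3. State how scores above each group's mild band are classed, so that every eligible patient has a severity value.
4. Derive severity from the raw MMSE score and the literacy definition before fitting the base-case model, rather than relying on a class entered at the site.

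The cost is small: a short text correction, one definition and an automatic recode. MMSE and education are already collected, so no new data are needed.

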### Sample size

The sample size was calculated using the equation, $$ n=\frac{U_{1-\alpha /2}^2{S}^2}{\delta^2} $$ where *S* was the stand division and *δ* was the allowable error. The planned sample size was generated based on previous data obtained from an economic evaluation of an AD-type dementia study [26]. Based on the standard deviation (SD) of AD-related costs per patient per year (11,037) and an allowable error of 500, the total sample size required was 1,872. Therefore, the planned total sample size in this study was ~2,500 to allow for a defective rate of 25%. Before starting the study, information was surveyed from all randomly selected participating sites, including the number of dementia physicians at each site, the number of AD patients, and the proportion of outpatients and inpatients in the last year. Based on these data 20–40 patients with AD will be assigned for each site. The sites include hospitals (Tier 3 hospitals, gerontology hospitals, mental health centres and psychiatric hospitals), nursing homes, gerocomiums, care facilities, and residences.

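### The sample size of 1,872 for an allowable error of 500 assumes independent patients, but 20–40 patients come from each of 81 sampled centres and no design effect is applied

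*Protocol article*

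**What the plan says.** The Sample size section uses n = U²S²/δ², with a standard deviation of 11,037 for annual cost per patient, and reports that for "an allowable error of 500, the total sample size required was 1,872". The only enlargement is for unusable records: "the planned total sample size in this study was ~2,500 to allow for a defective rate of 25" per cent. The section gives neither an ICC nor a design effect.

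The same section then describes a clustered intake: "Based on these data 20–40 patients with AD will be assigned for each site". The section on investigation sites says that sites were chosen at random within each region and that "The study included 81 research centres that meet the inclusion criteria". The title calls the study cluster-randomised. Nothing is allocated at random, so this can only mean that clusters were sampled at random.

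Under Calculation of costs due to AD, subgroups are compared by t-tests, "or Kruskal-Wallis analysis of variance will be used", with no mention of clustering. Later in that paragraph, in the description of the generalised linear model (GLM), the article says "we also added the sites as a covariant in the analysis".

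**The concern.** The formula gives the precision of one mean when patients are drawn independently. When patients are drawn in groups from sampled sites, and patients at one site resemble each other in cost, each further patient at that site adds less information. The variance of the mean then rises by the factor 1 + (m − 1) × ICC, where m is the number of patients per site.

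The article itself makes an ICC of zero hard to believe:

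- Under Total cost per patient per year, the time of informal caregivers without a stable job is valued at an average income reported by each research centre. Those patients at a centre therefore share a wage multiplier.
- The Discussion cites earlier work in which 84.9% of patients were cared for at home by non-professionals, so this component may be large.
- The Discussion also stresses economic differences between regions and cost differences between types of institution.
- Site is put into the model because the centres are diverse.

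The allowable error of 500 is the only precision the article states, and it concerns the study's main output, the mean annual cost per patient. If it is overstated, readers will place too much trust in that mean. A second consequence follows for P values: a test that ignores clustering rejects too often when the compared groups differ mainly by site.

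**Working it through.** **Inputs from the article.** S = 11,037; δ = 500 (no currency given); required n = 1,872; planned n about 2,500; defective rate 25%; 81 centres; 20–40 patients per site.

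**Assumptions.** Two-sided α = 0.05, since α is not stated. ICC from 0.01 to 0.10, since none is given. Site and research centre are treated as the same unit; this fits, because 2,500/81 = 30.9 lies within 20–40.

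**Step 1: reproduce the plan's figures.** 1.96² × 11,037² / 500² = 1,871.9, rounded up to 1,872. This confirms α = 0.05: 0.10 would give 1,319 and 0.01 would give 3,233. Then 1,872/0.75 = 2,496, or about 2,500. The whole enlargement is used up by the 25% allowance, and nothing is left for clustering.

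**Step 2: precision with clustering.** DEFF = 1 + (m − 1) × ICC; half-width = 1.96 × 11,037 × √(DEFF/n); effective n = n/DEFF.

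| ICC (assumed) | 1,872 evaluable, m = 1,872/81 = 23.1: DEFF; effective n; half-width | 2,500 evaluable, m = 2,500/81 = 30.9: DEFF; effective n; half-width |
|---|---|---|
| 0.01 | 1.22; 1,533; 552 | 1.30; 1,925; 493 |
| 0.02 | 1.44; 1,298; 600 | 1.60; 1,565; 547 |
| 0.05 | 2.11; 889; 726 | 2.49; 1,003; 683 |
| 0.10 | 3.21; 583; 896 | 3.99; 627; 864 |

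**Step 3: when does ±500 survive?** With all 2,500 evaluable, it needs DEFF ≤ 2,500/1,872 = 1.335, so ICC ≤ 0.335/(30.86 − 1) = 0.011. At ICC 0.01 and 81 centres, the patients needed per centre are 1,872 × 0.99 / (81 − 1,872 × 0.01) = 29.76, or about 2,410 evaluable in total. That allows the loss of about 90 of 2,500 records (under 4%), against the 25% planned for.

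**Step 4: can more patients per centre repair it?** With 81 centres, the effective n cannot exceed 81/ICC however many patients each contributes. Setting 81/ICC = 1,872 gives ICC = 0.043. At or above that value, ±500 is out of reach with 81 centres.

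**Step 5: subgroup tests.** For a factor constant within sites, a nominal 5% test that ignores clustering has actual size 2 × [1 − Φ(1.96/√DEFF)]. At m = 23.1 this is about 7.6%, 17.7% and 27.4% at ICC 0.01, 0.05 and 0.10.

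**The case against.** The strongest reply is that the article already deals with site differences by adding site to the GLM. This stands in part: the main model is not blind to site. But adjusting for site does not change the sample size calculation. Nor does it remove between-site variation from the sampling error of a mean meant to represent patients beyond these 81 centres. The adjustment is also not stated for the t-tests or Kruskal-Wallis tests.

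A second reply is that the shortfall rests on an assumed ICC. That is true, and it is why only a range is given. Site selection within all 30 regions may also remove some between-site variance, so the relevant ICC may be lower than a raw one. At 1,872 evaluable patients, however, any positive ICC gives a half-width above 500. A plan for slightly more than 2,500 patients, as the abstract has it, changes little.

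A third reply is that the aims are descriptive and that no point estimate changes. That is correct, and it limits the harm to stated precision and to P values.

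A reader might also infer several stronger points that the article does not support:

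- *All the unclustered tests are too liberal.* This is true for subgroups that vary mainly between sites, such as site type or region. For factors that vary within sites, such as sex or severity, ignoring clustering need not inflate the error and can be conservative. The article does not say which subgroups are compared.
- *Site enters as 81 fixed levels and so competes with urban or rural location.* The coding of site is not stated, and residence is listed as a patient characteristic that can vary within a hospital site.
- *The confidence intervals will be too narrow.* The article names no interval method and may leave it to the analysis plan.
- *There is an arithmetic error.* There is none; 1,872 is correct under its assumption.
- *Kruskal-Wallis is wrong because it compares ranks.* That is a separate question from clustering.

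**Conclusion.** The point holds as a fault in the design assumption. The article states a precision derived for independent patients, while its own design takes groups of 20–40 from sampled sites, and the only inflation is for defective records. At the 1,872 evaluable patients on which the claim rests, the half-width is about 552 to 896 for assumed ICCs of 0.01 to 0.10, which is 10% to 79% wider than the 500 stated.

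The shortfall is conditional, not certain. With all 2,500 evaluable and an ICC of at most about 0.011, ±500 is met.

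These figures rest on two-sided 95% confidence, equal numbers per centre, an unchanged standard deviation, an assumed ICC, and no credit for selection within regions. The conclusion on tests is limited to comparisons between groups that differ mainly by site.

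**What to change.** Keep the planned enrolment and make three changes.

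1. In the Sample size section, state a plausible ICC range with its source (the five-site pilot may help), and give DEFF = 1 + (m − 1) × ICC with 81 centres.
2. Restate the achievable precision as a range: about ±550 to ±900 at 1,872 evaluable patients for ICC 0.01–0.10, with the 2,500 figures (about ±493 to ±864) alongside. Keep the 25% allowance separate, for defective records only.
3. Specify cluster-aware standard errors, with site as the cluster, for the mean cost and for the subgroup comparisons. A site random intercept, GEE or a site-level bootstrap would each do. Say how site is coded in the GLM.

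The cost is wording in the protocol and analysis plan, a little more R code, and a less favourable stated precision. No extra patients are needed, provided the wider margin is accepted. If ±500 must be kept, Step 4 shows that above an ICC of about 0.043 it would take more centres, not more patients per centre.
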